### Intervention delivery

To minimize the potential effects of clinical bias and inadvertent contamination between the two interventions on the study outcomes [28], all therapists (two at each site) will administer each intervention in a randomized crossover fashion. Specifically, for the first half of the intervention study, one therapist will administer EBL and one therapist will administer ELL. For the last half of the intervention study, the therapists will switch over to administer the other type of intervention. Hence, therapists will administer both types of intervention, with a switch over approximately half way through the study. They will receive specialized training in the intervention type they are just about to administer. Using this approach, therapist effects will be balanced across the interventions [28]. Treatment fidelity will be monitored using a checklist based on Borelli’s framework [29,30]. Sessions will be audiotaped to enable therapists’ adherence to the treatment protocol to be examined for a random sample (20%) of sessions by experts who are independent of the study [30].

### Measures

The primary and secondary outcome measures and the timings of assessment are outlined in Table 3. The primary outcome measure assesses generalization of error self-regulation skills to a task distinct from but related to training (that is, meal preparation). Secondary outcome measures assess self-monitoring and self-regulation skills on a task unrelated to training, awareness of deficits, behavioral competency, role participation and supportive care needs.

**Table 3 T3:** Summary of outcome measures and the timing of assessment

**Outcomes measures**		**Pre-intervention use**	**Post**-**intervention use**	**6-month follow-up**
Primary	Cooking task	X	X	
Secondary	Zoo map test	X	X	
	Patient competency rating scale	X	X	X
	Awareness questionnaire	X	X	X
	Sydney psychosocial reintegration scale	X	X	X
	Care and needs scale	X	X	X

#### Primary outcome

The Cooking Task [21] is a 1-h naturalistic assessment task that involves independently baking a cake and making an omelet for two people. The task involves standard instructions, recipes, equipment and scoring. The total error score encompasses five error types and is the main score for analysis. Inter-rater reliability (>0.80 for all error types), test-retest reliability (*r* = 0.89), discriminant and convergent validity have been reported [21,31]. Audiovisual recording will be rated by blind assessors with inter-rater reliability examined on 20 % of randomly selected DVDs.

#### Secondary outcomes

The Zoo Map Test from the Behavioural Assessment of Dysexecutive Syndrome [32] is a standardized neuropsychological test which examines the ability to plan, monitor performance and follow rules. In part 1, participants are asked to independently formulate and implement a plan to follow a route through a map without breaking specific rules. In part 2, participants follow a predetermined plan to complete the route. Although the profile score (1 to 4) will be calculated, the part 1 score (sequence score minus total errors) is the main index for analysis because this more directly assesses self-monitoring and self-regulation skills. The Zoo Map Test has been found to be a reliable and ecologically valid measure of planning and self-regulation [32,33].

The PCRS [25] is a well-established measure of awareness deficits and behavioral competency after TBI. The 30 items on the PCRS relate to participants’ current level of competency on activities of daily living (for example, meal preparation), interpersonal skills (for example, initiating conversations), behavioral (for example, controlling temper) and emotional function (managing depression) and cognitive abilities (for example, remembering conversations). Items are rated on a five-point Likert scale (1 = ‘can’t do’, to 5 = ‘can do with ease’). The discrepancy score between self-ratings and informant ratings on the PCRS is calculated to provide an index of self-awareness. Relatives’ ratings on the PCRS will assess skills generalization or broader behavioral competency. The PCRS has good test-retest reliability (*r* >0.85) and internal consistency (α >0.90) and established validity, including sensitivity to change [34].

The Awareness Questionnaire (AQ) [35] is a 17-item scale that assesses awareness of deficits across sensory, physical, cognitive, and behavioral domains. Unlike the PCRS, ratings on the AQ compare participants’ post-injury abilities on each item to their pre-injury functioning (that is, 1 = much worse, 3 = about the same, 5 = much better). Positive discrepancy scores (participant minus relative ratings) indicate impaired self-awareness. The AQ has sound psychometric properties [35] and has demonstrated sensitivity to change in the context of awareness interventions [18].

The Sydney Psychosocial Reintegration Scale (SPRS; [36]) is a 12 item questionnaire that assesses level of psychosocial reintegration, or the ability of a person with brain injury to resume valued societal roles, including those of worker, driver, parent and spouse. The scale comprises three domains, and four questions for each domain. The three domains of the SPRS are: occupational activities, interpersonal relationships, and independent living skills. Excellent psychometric properties have been reported for the SPRS, including internal consistency (α = 0.90), inter-rater (intraclass coefficient (ICC) = 0.95) and test-retest (r = 0.90) reliability, construct validity, sensitivity, and support from Rasch analysis [36,37].

The Care and Needs Scale (CANS; [38]) measures the extent to which an individual can be left alone in the community, using a rating scale of 0 (‘Can live in the community, totally independently, does not need contact’) to 7 (‘Cannot be left alone, needs nursing care, assistance, and/or surveillance 24 hours per day’). The weekly hours of assistance required are also recorded. Psychometric properties, including inter-rater (ICC = 0.93 to 0.96) and test-retest (ICC = 0.98) reliability and construct, concurrent and predictive validity have been reported [38,39].

Ratings on the SPRS and CANS will be made by the blind assessors based on an interview with the relative (SPRS), and the participant and the relative (CANS) in accordance with the authors’ guidelines [36-39].

### Sample size

Our previous RCT findings [14,15] indicated that individualized EBL training was more effective than another active intervention in improving awareness of deficits and behavioral competency between pre-intervention and post-intervention assessment (group × time interaction effects: partial η^2^ = 0.061 to 0.13). Based on a similar design and approach to statistical analysis, a conservative power analysis was conducted using an estimated medium effect size (partial η^2^ = 0.061, PCRS discrepancy score), alpha level of 0.05, and power of 0.8. According to G*Power [40], a sample size of *n* = 123 is required to detect significant effects. Due to possible participant dropout (estimated as 10% from the previous RCT [14]), a total sample size of *n* = 135 will be required.

### Statistical analysis

Data will be screened to ascertain any state/site or therapist effects or the effects of demographic and clinical factors on outcome, with any significant variables treated as covariates in respective analyses. Participant dropout will be managed on an intention-to-treat basis using the last observation carried forward method, and participants will be analyzed in the group to which they were allocated, irrespective of compliance or withdrawal from treatment [41]. To compare the efficacy of EBL and ELL for improving error self-regulation skills, analysis of covariance (ANCOVA) will be conducted using endpoint means and adjusting for baseline scores for the primary outcome (Cooking Task errors) and secondary outcome (Zoo Map part 1). The estimated effect size and its precision will be examined using a 95 % CI for the mean difference. Mixed 2 × 3 analysis of variance (ANOVA) procedures (grouped by time: pre-intervention, post-intervention and follow-up periods) will examine the impact of each intervention on awareness of deficits, behavioral competency, role functioning and support needs. In the latter analyses, interaction effects will be examined to determine whether EBL is associated with greater gains than ELL relative to pre-intervention functioning. Hierarchical regression will be used to determine whether pre/post changes in awareness, error self-regulation and behavioral competency predict long-term outcomes on the SPRS and CANS after controlling for pre-intervention functioning.

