### Ethics and procedure

The ethical aspects of this research project have been approved by the Metro South Hospital and Health Service Human Research Ethics Committee (EC00167) and the ethics committees of the University of Queensland, and Griffith University, Queensland, Australia (HREC reference number: HREC/13/QPAH/096). After the first 6 months of data collection in Brisbane, ethical clearance for the project will be extended to the hospitals in Sydney to allow multisite participant recruitment. This project will be conducted in accordance with the National Statement on Ethical Conduct in Human Research (2007) produced by the National Health and Medical Research Council of Australia.

Informed consent will be obtained from each participant prior to commencement in the study. The independent and blind assessor will visit participants in their home to conduct the pre-intervention assessment, which will involve completing a series of questionnaires and neuropsychological tests (see Measures section below). The participant’s primary caregiver will also complete a set of questionnaires. Based on random allocation, participants will receive either the EBL or ELL intervention, both of which entail an 8-week home-based training program (one 90 to 120 minute session per week) with an occupational therapist (see Intervention section). A week after the final treatment session, the blind assessor will conduct a post-intervention assessment involving readministration of specific neuropsychological tests and questionnaires. At 6 months after the post-intervention assessment, the participant will be contacted by the blind assessor for a brief telephone-based assessment of their home and community functioning.

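### Site, therapist, demographic and clinical covariates enter each treatment model only if significant on the trial's own outcome, so the adjustment is not fixed in advance and therapist and the randomisation stratum may be left out

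*Protocol article*

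**What the plan says.** The Statistical analysis section of the protocol article sets a two-step rule. First, "Data will be screened to ascertain any state/site or therapist effects or the effects of demographic and clinical factors on outcome". Second, the result of that screen decides the model, "with any significant variables treated as covariates in respective analyses". The only adjustment fixed beforehand is the baseline score, in the ANCOVAs for Cooking Task errors (primary) and Zoo Map part 1. Awareness, competency, role functioning and support needs are analysed by mixed 2 x 3 ANOVA, with pre-intervention as one of the three time levels.

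The Randomization section allocates participants separately within two neuropsychological deficit subgroups. That stratum is not named as a term in any model.

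The Intervention delivery section places two therapists at each site: "for the first half of the intervention study, one therapist will administer EBL and one therapist will administer ELL". They exchange interventions at about the midpoint, and the article concludes that therapist effects will then be balanced. Ethics and procedure adds a staggered start: "After the first 6 months of data collection in Brisbane, ethical clearance for the project will be extended to the hospitals in Sydney".

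Under Sample size, "a sample size of *n* = 123 is required to detect significant effects", raised to 135 for 10% dropout.

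**The concern.** This is a rule that the article states, not a detail left to a later document. An analysis plan that followed it would inherit the problem. The additional covariates are picked by their p-values on the outcome being analysed, so the adjusted treatment effect and its confidence interval depend on a choice made after the data are seen. That choice can also differ between outcomes.

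Two of the terms left to chance follow from the design. Allocation is stratified by neuropsychological deficit, which the Trial design section regards as potentially related to functioning. At any one time at a site, arm and therapist coincide, and only the mid-study switch separates them. If the two periods at a site are unequal, part of the difference between its two therapists stays in the arm contrast. Whether the model removes it would depend on a screening test with limited power.

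**Working it through.** **Inputs.** From the article: N = 123 evaluable, partial η² = 0.061, alpha 0.05, power 0.8, 28 months of recruitment, three services in two cities and two therapists per site. That makes 4 therapists if a site is a city, or 6 if it is a service. Assumed, because the article gives no values: the screening threshold (0.05), therapist ICC, city difference and number of candidate factors.

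**The plan's own figure.** f² = 0.061/0.939 = 0.0650, so f = 0.255 and d = 2f = 0.51. An F test on 1 and N - 2 degrees of freedom with noncentrality N·f² = 123 × 0.0650 = 7.99 has power 0.801, and 122 participants fall just short at 0.797. The stated 123 is reproduced.

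**Chance that the screen finds a real therapist effect.** With J therapists, m = 123/J participants each and random therapist effects, power = P(F > Fcrit / [1 + m·ICC/(1 - ICC)]) on J - 1 and 123 - J degrees of freedom. For J = 4, m = 30.75 and Fcrit = 2.681. At ICC 0.05 the divisor is 1 + 30.75 × 0.05/0.95 = 2.618, so power = P(F > 1.024) = 0.385.

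| Assumed ICC | 4 therapists | 6 therapists |
|---|---|---|
| 0.02 | 0.182 | 0.161 |
| 0.05 | 0.385 | 0.363 |
| 0.07 | 0.491 | 0.483 |
| 0.075 | 0.514 | 0.510 |
| 0.10 | 0.612 | 0.625 |
| 0.20 | 0.819 | 0.866 |

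Detection passes one half at an ICC between 0.07 and 0.075.

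**City difference**, for splits from 50:50 to 75:25. A difference of 0.3 SD is found in 38% to 30% of trials, and one of 0.4 SD in 60% to 48%.

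**Chance entry of irrelevant factors.** With 6, 10 or 15 unrelated candidates, at least one enters with probability 1 - 0.95^k, that is 26%, 40% or 54%. Simulation gave 26%, 40% and 53%.

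**Type I error under the stated rule (simulation).** It is 5.0-5.3% with 6 to 15 unrelated candidates. With 6 therapists and an even switch, the screened, always-adjusted and never-adjusted models all give about 5%. With a 70:30 switch, the never-adjusted model gives 6.9% at ICC 0.05 and 9.2% at ICC 0.10. The screened model gives 5.4% at both, and always adjusting gives 4.7% and 5.0%.

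**Residual confounding from an uneven switch.** If a fraction p of a site's participants precede the switch, its arm contrast carries (2p - 1) times the difference between its two therapists. As an illustration, assume one switch at month 14, Sydney open from month 6, and uniform accrual at equal rates in the two cities. Then p = (14 - 6)/(28 - 6) = 8/22 = 0.364, and the carried share is 1 - 2 × 0.364 = 0.273. Therapists 0.4 SD apart would leave 0.273 × 0.4 = 0.11 SD in Sydney's contrast. Brisbane would be balanced. Sydney would supply 22/(28 + 22) = 0.44 of participants, so the pooled contrast would carry 0.44 × 0.11 = 0.05 SD, against a planned effect of 0.51 SD.

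**Cost of always including therapist (simulated power for d = 0.51, N = 123).** Power is 0.79 at ICC 0 with 4 or 6 therapists, 0.81-0.82 at ICC 0.05 and 0.82-0.83 at ICC 0.10. Without adjustment it is about 0.80 throughout.

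**The case against.** The strongest reply is that the rule does little inferential damage. Its type I error is about 5%, even with a 70:30 switch, because a large therapist effect tends to be caught. This stands. A reader might infer that the screen inflates false positives, and the calculations do not support that. Error rates above about 5.4% arise only if either the screened or the unadjusted result may be reported (5.3-5.9% with unrelated candidates, 7.1% with ten weakly prognostic ones). The article offers no such choice.

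A reader might also infer that real therapist or site effects will usually be missed. The article gives no ICC or site variance, and at ICC 0.10 the screen succeeds in 61-63% of trials. The statement holds only under the condition that the ICC is below about 0.07.

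Nor does the later Sydney start show that the design is unbalanced. The article fixes no month for the switch and does not say whether it is common to all sites. If the midpoint means half of all participants at equal city rates, then t + (t - 6) = 25 gives t = 15.5 months. Sydney's share before the switch becomes 9.5/22 = 43%, and the carried share is 14% rather than 27%.

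Finally, the primary model is largely specified: ANCOVA on endpoint with baseline adjustment. Only the additional covariates are open. The exact candidate list and threshold may properly sit in a fuller document, so their absence here is no criticism.

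What survives is the rule itself, which makes entry depend on significance, outcome by outcome, for terms that the design already singles out.

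**Conclusion.** The point holds in a limited form. The stated rule makes the additional covariates data-driven and possibly different for each outcome, and it can leave out therapist and the randomisation stratum. Non-significance is poor evidence for omitting them when the assumed therapist ICC is below about 0.07. Above that, the screen works more often than not.

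The harm is moderate: an adjusted estimate that is not fixed before the data are seen, some loss of precision when a prognostic term is omitted, and possible residual therapist confounding if the switch is uneven within a site. The loss of precision is small for therapist: at 4 therapists and ICC 0.10, power is 0.822 with the screen and 0.826 with therapist always included. The illustrated confounding, about 0.11 SD in Sydney and 0.05 SD pooled, rests wholly on the assumed switch date, start date, accrual pattern and therapist difference. It shows scale and is not a prediction. The change is worth making because it is specific and costs almost nothing.

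**What to change.** Delete the significance screen and name the terms in advance.

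- **Cooking Task and Zoo Map ANCOVAs:** baseline score, neuropsychological deficit stratum, and therapist nested in site (which absorbs site and city), all kept whatever their p-values.
- **Mixed 2 x 3 analyses:** stratum and therapist, each with its interaction with time. Do not add baseline as a covariate, because pre-intervention is already a time level.
- **Any other demographic or clinical factor:** a labelled sensitivity analysis only.
- **Intervention delivery:** state that the therapist switch is made within each site, at about half of that site's participants. This needs a working recruitment target per site, which the article does not give.

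The cost is 3 degrees of freedom for 4 therapists or 5 for 6, plus 1 for the stratum in each ANCOVA. In the simulations of the therapist terms, that is about 1 point of power if therapists do not differ (0.79 against 0.80). The sample size stays at 123 evaluable and 135 randomised.

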## Discussion

TBI is a leading cause of lifelong disability that mainly affects young people at the start of their independent and working lives. Impairments in self-awareness and self-regulation greatly undermine people’s ability to live independently and re-enter the workforce. By comparing the efficacy of EBL and ELL this project will determine the benefits of training internal self-regulation strategies after severe TBI. The findings are expected to have important theoretical and practical implications for treatment approaches that can potentially be used to enhance individuals’ everyday functioning and reduce the personal and social burden of TBI in the community.

Traditionally, rehabilitation trials have focused on increasing or decreasing target behaviors on a specific task (for example, remembering steps to pay a bill). An issue that has typically been neglected is whether training generalizes beyond the therapy context [11]. Lack of skills generalization poses one of the biggest barriers to successful outcomes of rehabilitation after a TBI. This study seeks to determine whether it is beneficial for people with severe TBI to make errors as they learn or relearn skills in rehabilitation. It will also examine whether immediate post-training gains translate to improved long-term functional outcomes, which is the ultimate goal of rehabilitation. In doing so, the project will clarify the role of errors in task learning and generalization. Addressing these research priorities represents the key innovations of the present RCT, and the findings are expected to revise and guide clinical practice in neurorehabilitation.

The main methodological challenge in this study relates to retention of participants over the 6-month follow-up period. To enhance retention success we will obtain multiple points of contact from participants. The use of telephone-based assessment has been found to be well accepted by people with TBI and their relatives, and is more effective and economical than postal return of questionnaires and home-based assessments respectively [42]. Overall, the feasibility of the assessment and intervention procedures employed in this study is supported by our pilot research [15,16,18].

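### Last observation carried forward scores every missing Cooking Task or Zoo Map endpoint as exactly zero change; it shrinks the expected EBL effect, and can bias it either way if both arms improve and dropout is unequal

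*Protocol article*

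**What the plan says.** The protocol article names one method for missing data, in Statistical analysis: "Participant dropout will be managed on an intention-to-treat basis using the last observation carried forward method". The same section says participants are analysed in the arm to which they were allocated.

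The primary analysis is described as follows: "analysis of covariance (ANCOVA) will be conducted using endpoint means and adjusting for baseline scores for the primary outcome (Cooking Task errors"; Zoo Map part 1 is handled the same way. Table 3 ("Summary of outcome measures and the timing of assessment") marks these two measures at pre- and post-intervention only. Ethics and procedure makes the 6-month contact a "brief telephone-based assessment of their home and community functioning", so no later Cooking Task can exist. The PCRS, AQ, SPRS and CANS are marked at all three visits and go into 2 × 3 mixed ANOVAs.

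A hierarchical regression then asks whether "pre/post changes in awareness, error self-regulation and behavioral competency predict long-term outcomes on the SPRS and CANS after controlling for pre-intervention functioning". The Discussion adds: "The main methodological challenge in this study relates to retention of participants over the 6-month follow-up period".

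**The concern.** With two scheduled measurements, carrying forward means copying the baseline score into the endpoint. That score is also the ANCOVA covariate. Everyone without a post-intervention Cooking Task is therefore analysed as if it had been repeated with an identical result. Analysing people as randomised does not require this.

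The assumption is least plausible in the arm expected to improve, which is EBL. If ELL participants also do better the second time, for example through practice, the arm that loses more people is penalised more, and a difference in dropout turns into a difference in outcome.

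For the three-visit scales, anyone lost after the post-intervention visit is given perfect maintenance over the interval the trial wants to study. In the regression, a person lost before the post-intervention visit and never reached again enters with a predictor change of zero and 6-month SPRS and CANS scores equal to baseline. That is an artificial data point that agrees with the hypothesis.

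**Working it through.** **The plan's own figure.** Sample size gives "partial η^2^ = 0.061, PCRS discrepancy score" with "alpha level of 0.05, and power of 0.8". Then f² = 0.061/0.939 = 0.0650, f = 0.255 and d = 2f = 0.51. The two-group noncentral F test with λ = f²N has power 0.7975 at N = 122 and 0.8007 at N = 123, so the stated 123 is reproduced. Adding 10% gives 123 × 1.10 = 135.3, the stated 135. The sample size is not at fault.

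**Inputs.** From the article: 135 randomised, 10% dropout, d = 0.51 (taken as residual SDs), and Cooking Task test-retest r = 0.89, used as the upper pre-post correlation. Assumed: 1:1 allocation (68 and 67), a lower correlation of 0.5, common gain g in both arms (0, 0.3 or 0.5 outcome SD), the dropout split by arm, and random dropout within arm.

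**Expected LOCF estimate.** Let dE and dL be the dropout shares in EBL and ELL, and s = √(1 − r²) the residual SD, which is 0.866 at r = 0.5 and 0.456 at r = 0.89. Dropouts contribute zero change, so the LOCF contrast is (1 − dE) × EBL gain − (1 − dL) × ELL gain. In residual SDs:

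LOCF estimate = (1 − dE) × 0.51 + (dL − dE) × g/s

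- 10%/10%, any g: 0.90 × 0.51 = 0.46.
- 15% EBL/5% ELL, g = 0: 0.85 × 0.51 = 0.43.
- 5% EBL/15% ELL, g = 0: 0.95 × 0.51 = 0.48.
- 15%/5%, r = 0.5, g = 0.3: 0.4335 − 0.10 × 0.3/0.866 = 0.40.
- 15%/5%, r = 0.89, g = 0.5: 0.4335 − 0.10 × 0.5/0.456 = 0.32.
- 5%/15%, r = 0.5, g = 0.3: 0.4845 + 0.035 = 0.52.
- 5%/15%, r = 0.89, g = 0.5: 0.4845 + 0.110 = 0.59.

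**Power and type I error**, by simulation of the baseline-adjusted ANCOVA (20,000 runs per scenario; ranges cover both correlations and, where shown, both gains):

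| Common gain | Dropout EBL/ELL | LOCF power | Observed-case power | LOCF type I error |
|---|---|---|---|---|
| 0 | 10%/10% | 0.78-0.79 | 0.79-0.80 | 5% |
| 0 | 15%/5% | 0.73-0.74 | 0.79 | 5% |
| 0.3-0.5 SD | 10%/10% | 0.71-0.76 | 0.79 | 5% |
| 0.3-0.5 SD | 15%/5% | 0.42-0.64 | 0.79-0.80 | 6% (r = 0.5), 7-10% (r = 0.89) |
| 0.3-0.5 SD | 5%/15% | 0.86-0.91 | 0.79 | 5-7% (r = 0.5), 7-10% (r = 0.89) |

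Observed-case ANCOVA stayed at 0.51 with type I error of about 5% throughout. The model standard error under LOCF matched the empirical SD of the estimate in every scenario (for example 0.167 and 0.168). The fault in the primary analysis is bias.

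**Long-term regression.** With a true slope of zero and 10% lost before the post-intervention visit and not reached later, LOCF gave false-positive rates of 11% with moderate mean gains, 31% with larger ones, and about 6% (no bias in the slope) when mean gains were zero. With 5% lost early and 5% late, the two non-zero settings gave 7% and 12%. Observed cases stayed at 5-6%. All parameters here are assumed. The direction follows from the geometry: a point at zero change and zero gain lies below both means and pulls the slope upwards.

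**The case against.** The strongest reply is that on the article's own terms the damage is small. Table 1 expects ELL to produce minimal change on untrained tasks. With g = 0 the term that can favour EBL vanishes: LOCF only pulls the effect towards zero, and balanced 10% dropout costs one or two points of power. Ten per cent may also overstate losses on the Cooking Task, because the Discussion places the main retention problem in the 6 months after that task is finished. This stands, and it limits the size of the problem in the expected case. It does not defend the method, since the article cannot guarantee zero ELL gain or balanced dropout.

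Four stronger readings are tempting, and the documents do not support them.

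- *LOCF inflates type I error.* Under random dropout it does so only with unequal dropout and a common gain together. The article gives 10% overall, with no split by arm.
- *LOCF favours EBL.* An exaggerated effect needs both a real ELL gain, which Table 1 does not expect, and higher ELL dropout.
- *The standard errors are wrong.* For the primary ANCOVA they were not, in any scenario checked.
- *Every dropout becomes a no-change, no-gain pair in the regression.* Only people lost before the post-intervention visit and not reached at 6 months do. Those lost later keep their true pre/post change and have only the 6-month outcome filled in.

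**Conclusion.** The concern holds in bounded form. The article fixes LOCF as the way dropout is handled, and its own visit schedule turns that into baseline carried forward for the primary outcome and the Zoo Map. This does not depend on anything an unseen analysis plan might add.

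In the expected case the cost is a shrinkage equal to the EBL dropout share, about 10% as planned, with almost no loss of power and no type I inflation. Under unequal dropout with gains in both arms, the estimate can move to 0.32-0.40 or 0.52-0.59 against a true 0.51. Those figures rest on the assumed 15%/5% split and 0.3-0.5 SD common gain. The carried-forward 6-month values and the regression artefact affect secondary analyses; the size of the latter depends on assumed parameters and cannot be fixed from the article.

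**What to change.** Replace LOCF as the main method, before any unblinded analysis.

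- **Cooking Task and Zoo Map:** baseline-adjusted ANCOVA on observed post-intervention scores, or multiple imputation by arm.
- **PCRS, AQ, SPRS and CANS:** a likelihood-based repeated-measures model using all available visits.
- **Hierarchical regression:** no carried-forward values, in predictors or outcomes.
- **Keep** the rule of analysing participants as randomised. LOCF may stay as a sensitivity analysis.

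The cost is revised wording and a little more programming, with no extra participants or visits. The drawback is that the replacement relies on data being missing at random given the variables in the model. That should be stated openly; it is weaker than assuming that everyone who leaves stays exactly where they were.
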